### Outcome measures

#### Primary outcomes

In the current study, the primary outcome is the changes in health assessment quality (HAQ) score from baseline values.

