#### Secondary outcomes

Secondary outcomes are the changes in erythrocyte sedimentation rate (ESR), C-reactive protein (CRP), disease activity score in 28 joints (DAS-28), Visual Analogue Scale pain intensity (VAS-pain), level of total oxidant and antioxidant capacity (TOC and TAC), oxidative stress index (OSI), tender joint count (TJC), swollen joint count (SJC), tender-swollen joint count difference (TSJD), morning stiffness count (MS), patient global assessment of disease activity (PGA), global assessment of disease activity (EGA), and clinical disease activity index (CDAI) from baseline values.

We will evaluate both primary and secondary outcomes two times, first after the run-in period, at the beginning of the intervention, and second, 8 weeks later.

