### Study sample size calculation

Considering that the primary goal in this study is to improve clinical symptoms in the IF group compared to the normal diet (HAQ score is considered as the primary outcome in this study), the number of samples required to conduct this study based on the change in HAQ, the IF group compared to the usual diet by 0.68 (a minimum clinically important difference), and considering the test power of 80%, the type I error is equal to 0.05, and the standard deviation is 0.6 was calculated for the result of 20 people in each group. We used SPSS software for calculation.$$n=2\times \frac{{\left({z}_{1-\frac{\alpha }{2}}+{z}_{1-\beta}\right)}^2}{\Delta ^2}\ S2$$$${n}=2\times \left[{\left(1.96+0.84\right)}^2\times \right(\left(0/{6}^2\right)\Big]/{(0.68)}^2$$

*n* = sample size in each group

*a* = type I error = 0.05

*b* = Power = 0.80

*S*
^2^ = standard deviation of the studied result (SD)

Δ^2^ = minimal clinically important difference

Therefore, considering a 10% chance of dropping out, the final sample size will be 44 people (22 people in each group) [54].

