### Statistical analysis

Analyses will be performed according to the intention-to-treat analysis (ITT) method. Therefore, all participants who entered the study (regardless of whether they completed the 8-week study period) are included in the analysis. In people who will have a drop, the last data will be used. Then re-analyses will be performed based on the protocol-based analysis method (per protocol analysis), so that the changes in the results can be seen. Patients who finished the 8-week duration of the study and were visited by the researchers will be included in the per-protocol analysis. Descriptive and analytical statistics will be used for data analysis and all analyses will be done in SPSS version 24 software. The normal distribution of the variables will be checked through the scatter plot, histogram, and Shapiro-Wilk test. Variables with non-normal distribution will be reported as median (interquartile range). The mean (standard deviation) will be employed to quantify quantitative variables, while a frequency report (percentage) will be used to characterize qualitative variables. A comparison of absolute or relative frequency is done using the chi-square statistic. Between-group differences in trial results will be evaluated using a general linear mixed model for continuous variables and a chi-square test for categorical variables. Based on this, the significance will be defined in values of *P* less than 0.05 and *q* less than 0.1. Cohen’s changes will be calculated based on the mean and standard deviation, and based on that, the effect size (0.20, 0.50, and 0.80, respectively, low, medium, and high therapeutic effect) of dietary intervention will be determined. Also, a *P*-value < 0.05 will be considered statistically significant in all analyses.

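### The Statistical analysis section gives two conflicting significance rules for between-group results; the conflict falls mainly on the 14 secondary outcomes, and on HAQ only if it belongs to the undefined q family

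*Protocol article*

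**What the plan says.** All of the conflicting text is in one paragraph of the protocol article, under Statistical analysis.

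- The analysis sentence: "Between-group differences in trial results will be evaluated using a general linear mixed model for continuous variables and a chi-square test for categorical variables".
- The next sentence builds on it and sets a joint criterion: "the significance will be defined in values of *P* less than 0.05 and *q* less than 0.1". It does not say what q is, how it is computed, which outcomes it is computed over, or whether the primary outcome is among them.
- The paragraph closes with a criterion that has no q condition: a P-value below 0.05 "will be considered statistically significant in all analyses".

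Three other places matter. Under Primary outcomes there is a single primary: "the primary outcome is the changes in health assessment quality (HAQ) score from baseline values". Under Secondary outcomes there are 14 changes from baseline: ESR, CRP, DAS-28, VAS-pain, TOC, TAC, OSI, TJC, SJC, TSJD, MS, PGA, EGA and CDAI. Under Study sample size calculation the trial is sized on P alone: "the type I error is equal to 0.05, and the standard deviation is 0.6".

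**The concern.** Both sentences cover between-group results, and they cannot both be the decision rule. The first lets a secondary finding count only if it also passes a q threshold, which would limit false positives across a long list. The last lets every nominal P<0.05 count.

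This matters because the Study hypothesis section covers inflammation and oxidative stress as well as quality of life and symptoms. Those two claims rest on secondary outcomes (ESR, CRP, TOC, TAC, OSI), so the choice of sentence decides whether they carry any multiplicity control. The trial is also unblinded for patients, doctors and researchers (Randomization section). A threshold left open could be settled after results are known.

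**Working it through.** The plan gives no error rate for either rule, so there is no stated figure to reproduce on this point.

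**Inputs.** Rule A: P<0.05 and q<0.1. Rule B: P<0.05. Both are from Statistical analysis. Number of secondary outcomes: 14, counted from Secondary outcomes. Assumption: q is a Benjamini-Hochberg q-value, that is, P × m / rank, made monotone, for m tests.

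**Where the rules differ.** Rule A is nested in rule B.

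| Result | Rule A | Rule B |
|---|---|---|
| P≥0.05 | not significant | not significant |
| P<0.05 and q<0.1 | significant | significant |
| P<0.05 and q≥0.1 | not significant | significant |

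Only the third row is in dispute.

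**Secondary outcomes under rule B, no true effect.**
- Expected false positives: 14 × 0.05 = 0.7.
- Chance of at least one, independent tests: 1 − 0.95^14 = 0.512, about 51%.
- Independence does not hold. Under Assessment of inflammation and pain, DAS-28 is computed from TJC, SJC, CRP and a patient VAS, and CDAI from TJC, SJC, PGA and EGA. OSI is TOC divided by TAC, and TSJD is the tender-swollen difference. A simulation with 22 per arm, ten base variables and these four derived from them (normality and weights assumed) gives about 45% with uncorrelated base variables, 34% at correlation 0.5 and 28% at correlation 0.7.

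**Secondary outcomes under rule A, no true effect.**
- Chance of at least one: about 10% with independent tests, by simulation.
- A lone smallest P among 14 needs P < 0.10/14 = 0.0071.

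**How often the rules disagree.** In a simulation of 15 outcomes (HAQ plus 14) with no true effect, they disagree on at least one outcome in about 48% of trials with independent outcomes and 32% at correlation 0.5.

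**Primary outcome, conditional on family.**
- HAQ as a family of one: q = P × 1/1 = P. Rules A and B agree.
- HAQ in a family of 15, P = 0.03, no other small P: q = 0.03 × 15/1 = 0.45. Rule A fails, rule B passes.
- Same P = 0.03 as the fifth smallest, none of the larger P-values giving a lower q: q = 0.03 × 15/5 = 0.09, passes. As the fourth smallest, with the others large: 0.03 × 15/4 = 0.1125, fails.
- Power for HAQ in a family of 15, using the stated difference of 0.68, SD of 0.6 and 20 per group, with no secondary effects and independent outcomes: about 95% under rule B and 82% under rule A (simulation). The 20 per group is taken as stated; its derivation is not part of this point.

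**The case against.** The strongest reply is that this is loose drafting. The q sentence follows directly from the between-group model, while the closing sentence begins as an addition and could be meant as a general alpha for everything else, such as frequency comparisons or the per-protocol re-analysis. That may well be the intent, and nothing shows a deliberate withdrawal of the q criterion. But the closing sentence is worded to cover all analyses, so the literal text still gives two verdicts.

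A second reply is that the q method and its family are details commonly left to an analysis plan, and that unadjusted secondary outcomes beside a single primary are a defensible choice. Both are fair. The absence of a definition of q is not the finding, and either rule alone could be defended. An unseen plan cannot, however, make both published sentences true.

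A reader might also infer that the primary verdict is itself left open. The documents do not support that. They never place HAQ in a q family, they name one primary outcome, and they size the trial on a type I error of 0.05 with no q condition. The wording does not exclude HAQ either, so the point stays conditional. The q = 0.45 example is an extreme case even then.

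Finally, 51% should not be read as this trial's error rate. It is the independent-test ceiling, and the visible overlap among outcomes puts the figure below it.

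**Conclusion.** The contradiction is real and stands in the current text, but its reach is limited. It changes the verdict only for results with P<0.05 and q≥0.1, chiefly among the 14 secondary outcomes. For those, with no true effect, the choice of sentence moves the chance of at least one false positive between at most about 51% (roughly 28–45% under the assumed dependence) and about 10%.

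The 10% and the 0.0071 threshold rest on q being a Benjamini-Hochberg q-value over the outcomes considered, and the 28–45% on assumed correlations, weights and normality. The existence of two rules is certain. Any effect on HAQ depends on a family membership that the protocol does not state.

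**What to change.** State one rule before the data are seen:

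1. Test the HAQ outcome alone at two-sided P<0.05, outside any q family. This matches the type I error used in the sample size section.
2. Apply a named false discovery rate method, for example Benjamini-Hochberg, at q<0.10 across the 14 listed secondary outcomes.
3. Delete the closing P<0.05 sentence, or restrict it so that it does not override the q rule.

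The contradiction does not require relabelling the per-protocol, effect-size or anthropometric analyses. The change is an edit of about two sentences, with no effect on conduct or sample size. Its cost is that fewer secondary outcomes may be called significant.

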### Interim analyses

Given the lack of any adverse effects observed in prior studies, no interim analysis or stopping rules are expected to be necessary for our current study of the IF diet.

*Plans to give access to the full protocol, participant-level data and statistical code*

It is possible to access the full details of the study protocol through IRCT.ir (IRCT20230217057441N1). The corresponding author can provide access to the data and participant datasets that were analyzed during the study.

### Frequency and plans for auditing trial conduct

There is no plan to audit the relevant tests in this study. The principal investigator should ensure that the trial steering committee and the ethics committee are kept informed of any potential risks that may arise during the course of the study.

### Plans for communicating important protocol amendments to relevant parties (e.g., trial participants, ethical committees)

In the event of any substantial changes that could affect the conduct of the trial or patient safety, we will keep the Trial Steering Committee and all participants informed and document any deviations from the trial protocol using a breach report form. Additionally, edited versions of the study protocol will be made available on the Iranian Registry for Clinical Trials (IRCT.ir) for public viewing.

## Discussion

Previous studies show the effect of IF regimes on improving performance and strong resistance to a wide range of destructive mechanisms, including those that include metabolic and oxidative stress [55]. Insulin acts as the main stimulating hormone in the satiety state, glucagon acts as the main hormone in the fasting state, and the body uses the liver’s glycogen reserves to produce energy during fasting [56]. In the IF diet, a person repeatedly experiences satiety and hunger and the onset of negative energy balance in IF is when liver glycogen reserves are depleted, insulin levels decrease, glucagon levels increase, and fatty acids are metabolized to produce energy, which is usually more than 12 h after stopping food consumption and leads to autophagy, reduction of oxidative stress, improvement of metabolism, and increase of life span [57–59]. An umbrella study of meta-analyses conducted on the results of this type of diet on various factors showed improvements in CRP, TNF, and IL-6 factors in these patients [60]. A study by Uden et al. aimed at investigating the clinical performance of individuals and blood neutrophils in patients with RA after 7 days of complete fasting was conducted on 26 affected women and the results of this study showed a significant relationship between improving the inflammatory activity of joints and increasing the bactericidal capacity of neutrophils [58]. Also, a study that was conducted in 2010. The purpose of this study was to explore the alterations in intestinal microflora in individuals with RA when following a fasting or Mediterranean diet was conducted on 50 people with RA, and patients in the fasting group received about 300 calories during 7 days and the results of this study showed a significant decrease in the average score DAS-28 in both groups. Also, this study states that more studies are needed in the field of induced changes in fasting diet in patients with RA [59]. Moreover, a study was conducted to examine the effects of fasting or a ketogenic diet on serum levels of interleukin-6 and dehydroepiandrosterone sulfate in patients with RA. The results showed in addition that fasting had a positive effect on the serum levels of the investigated cases, and menopause as a confounding variable had an effect on the results of this study [29]. As noted, a large number of studies to evaluate the relationship between fasting and RA have investigated complete fasting, no food intake, or calorie restriction [27, 29, 30]. Despite the short-term positive effects of full or partial fasting with calorie restriction, this type of fasting is an impractical long-term strategy, as it should not be sustained for more than 7 days because it causes malnutrition in patients and its short-term positive effects are fleeting compared to the chronic nature of RA. Clinical and laboratory measurements tend to show improvement within a few days of beginning a fast and worsen upon resumption of diet and intake of restricted foods. Therefore, although many studies have been conducted on the effects of complete or partial fasting with caloric restriction in patients with RA and the results of them showed the overall positive effect of fasting on the symptoms of RA, considering the limitations of complete fasting in the form of no food intake or limiting calorie intake, and mentioning that until today, no study has been conducted to investigate the effects of IF in these patients in the world and Iran, this study will be conducted.

### Strengths and limitations

This study is the first clinical trial that evaluates the effects of IF on quality of life, clinical symptoms, inflammation, and oxidative stress in overweight and obese postmenopausal women with RA. This cost-effective intervention can be readily implemented in clinical settings. if the results of this study showed improvement in symptoms in these patients, after evaluation and acceptance of the next studies, it can be used to manage and improve the symptoms of RA patients. Another strength of this study is the block matching of patients in terms of several variables that may affect the findings of the study. Also, at the start and end of the study, we will assess biochemical markers, as well as subjective and objective symptoms in patients. Compliance with the intervention will be assessed throughout the study.

The limitation of this study is we just evaluate the effects of IF in menopausal women, because of limitations in block matching and there is a need for more studies to evaluate IF in other groups of patients who suffer from RA. In addition, the potential for subjective judgments to influence the evaluation of outcome variables should be taken into consideration.

### Trial status

Ongoing, protocol version: 1; 2023-03-05: This study’s recruitment period is slated to take place from July 24, 2023, to December 2023.

### Patient and public involvement

The public and patients were not consulted during the formation of the research question, implementation of the study, recruitment of participants, execution of the study, or reporting of the results. The results of the study will be published to the study participants at the end of the study using social media.

## Data Availability

Not applicable.

## Abbreviations

RA: Rheumatoid arthritis
IF: Intermittent fasting
BMI: Body mass index
NSAIDs: Nonsteroidal anti-inflammatory drugs
HAQ: Health Assessment Questionnaire
ESR: Erythrocyte sedimentation rate
CRP: C-reactive protein
DAS-28: Disease Activity Score-28
VAS-pain: Visual Analogue Scale pain intensity
TOC: Total oxidant capacity
TAC: Total antioxidant capacity
OSI: Oxidative stress index
TJC: Tender joint count
SJC: Swollen joint count
TSJD: Tender-swollen joint count difference
MS: Morning stiffness count
PGA: Patient global assessment of disease activity
EGA: Global assessment of disease activity
CDAI: Clinical disease activity index
ACR: American College of Rheumatology
RF: Rheumatoid factor
ACPA: Anti-citrullinated protein antibodies
DMARDs: Disease-modifying antirheumatic drugs
HAQ-DI: Health Assessment Questionnaire-Disability Index
ELISA: Enzyme-linked immunosorbent assay
SPIRIT: Standard Protocol Items Recommendations for Interventional Trials
